### Randomisation of practices

The study is cluster-randomised, with all enrolled participants in one practice randomised to one arm of the trial in order to avoid potential 'contamination' from participants randomised to different arms. Randomisation was carried out independently at the University of Leicester, after stratification for practice setting and list size. Two randomisation plans were computed, one for small and one for large lists sizes. ^a^Practices agreed to participate in the study before being randomised. Practices were not informed of their randomisation when recruited, but become aware of it during the study as participants attend the practice for clinical support and repeat prescriptions for monitoring resources.

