### Referral and recruitment of participants

Practice nurses referred people who were newly diagnosed with T2DM and interested in participating in the study to the local DESMOND team. A member of the local DESMOND team then contacted each individual referral to confirm eligibility and check readiness to participate; if willing the individual was booked to attend an appropriate DESMOND programme. Practice nurses and DESMOND co-ordinators were instructed not to tell individuals which type of course they would be attending.

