### Analysis

#### Power calculations and sample size

The aim is to show equivalence in mean HbA1c at 18 months of within ± 0.5%. Assuming a standard deviation (SD) at 18 months of 1.5%, [37] the sample size required without allowing for clustering for 80% power at 5% significance is 142 per arm. With an intra-cluster correlation of 0.05, [38] and an expected mean cluster size of 5, adjustment for clustering brings the number required to 170 per arm. Assuming 20% drop out and 20% non-consent, the numbers required are 266 referrals and 213 consents per arm.

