#### Statistical analysis

There will be double entry of all data and discrepant values will be investigated. Results will be reported according to CONSORT guidelines for cluster randomised trials and statistical analysis carried out on an intention-to-treat basis. Missing outcomes will not be replaced and an average over-time of continuous outcomes will be derived. This procedure will measure the cumulative effect of the treatment and have the maximum number of participants. Continuous variables will be analysed using a linear model adjusting for clustering using generalised estimating equations, and adjusting for baseline values.

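### The sample size allows for clustering by practice only, although teaching is in arm-specific group courses that very probably mix practices; if the analysis does the same, the equivalence interval would be too narrow

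*Protocol article*

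**What the plan says.** **Randomisation.** The unit is the practice, with "all enrolled participants in one practice randomised to one arm of the trial" (*Randomisation of practices*). The *Discussion* confirms that level. There are 75 practices (*Involvement of practice nurses*) in 8 sites (*Methods/Design*).

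**Delivery.** Participants must be able and willing to join a group programme and must attend within 6 months of diagnosis (*Patient eligibility criteria*). Practices refer to the local DESMOND team, which contacts each person; "if willing the individual was booked to attend an appropriate DESMOND programme" (*Referral and recruitment of participants*). The same section shows that course type depends on arm. Two educators lead the programme (*Study intervention*), and at its second meeting participants discuss their monitoring experience (*Methods of self-monitoring*).

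**Sample size** (*Power calculations and sample size*). "The aim is to show equivalence in mean HbA1c at 18 months of within ± 0.5" percent. The unadjusted figure is 142 per arm, then: "With an intra-cluster correlation of 0.05, [38] and an expected mean cluster size of 5, adjustment for clustering brings the number required to 170 per" (the figure is for each arm). No term for course or educator appears.

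**Analysis** (*Statistical analysis*). A linear model is planned, "adjusting for clustering using generalised estimating equations". The unit of clustering is not named.

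**The concern.** People taught in the same course share educators, peers and discussion. *Training of educators* itself recognises that educators' views of the two methods could affect delivery and so the result. If course-mates come from different practices, a variance that clusters on practice treats them as independent. Each course belongs to one arm, so course-level variation specific to an arm goes into the difference between arms.

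In an equivalence trial the direction of this error matters. An interval that is too narrow fits inside ±0.5% more easily, so equivalence is declared too often. *Implications of the hypothesis* says that a finding of equivalence would be used to recommend blood monitoring in this group.

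**Working it through.** **1. Reproducing the plan's figures.** Inputs from *Power calculations and sample size*: margin 0.5, SD 1.5, power 80%, significance 5%, ICC 0.05, mean cluster size 5.

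- Unadjusted: n = 2 × [1.5 × (1.960 + 0.842) / 0.5]² = 141.3, so 142.
- Design effect (DE): 1 + (5 − 1) × 0.05 = 1.20.
- Adjusted: 142 × 1.20 = 170.4, stated as 170.
- Consents: 170 / 0.8 = 212.5, so 213. Referrals: 213 / 0.8 = 266.25, so 266.

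All four figures reproduce with a single level of clustering. (Whether this formula suits an equivalence test is a separate question.)

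**2. Which level is it?** Consents per practice: 2 × 213 / 75 = 5.7. Analysed per practice: 2 × 170 / 75 = 4.5. A mean size of 5 lies between them, so the cluster is the practice.

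**3. Do courses mix practices?** The article does not say. The evidence is indirect:

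- Practices per site: 75 / 8 = 9.4.
- A practice yields about 5.7 consents over the whole of recruitment, and each person must attend within 6 months of diagnosis. Courses drawn from one practice would usually be very small.
- Booking is done by the local team, not by the practice.

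Mixing is therefore very probable, but its extent is unknown.

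**4. Effect of a course-level correlation.** The documents give neither course size nor course ICC. Assumed: m = 6 to 10 analysed per course, course ICC ρ = 0.01 to 0.05, and all course-mates from different practices (the worst case). Then

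DE = 1 + (5 − 1) × 0.05 + (m − 1) × ρ,

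and the interval should be wider than a practice-only interval by the factor √(DE / 1.20). Required n is 142 × DE, rounded up. Power uses the plan's own formula with 170 / DE effective participants per arm. Coverage is that of a nominal 95% practice-only interval.

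| m | ρ | DE | Width factor | Coverage | Power at 170 per arm | n per arm needed |
|---|---|---|---|---|---|---|
| any | 0 | 1.20 | 1.00 | 95% | 80% | 170 (as planned) |
| 6 | 0.01 | 1.25 | 1.02 | 94.5% | 78.5% | 178 |
| 8 | 0.02 | 1.34 | 1.06 | 93.6% | 75.6% | 191 |
| 10 | 0.05 | 1.65 | 1.17 | 90.5% | 66.7% | 235 |

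When the true difference lies at one margin, the chance of passing that margin rises from 2.5% to between 2.7% and 4.7% over the same range.

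**5. Sensitivity to the meaning of course size.** If 6, 8 and 10 are consented attendees, 20% drop-out leaves 4.8, 6.4 and 8 analysed. The three width factors become √(1.238 / 1.20) = 1.02, √(1.308 / 1.20) = 1.04 and √(1.55 / 1.20) = 1.14.

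**The case against.** The other side has several fair points.

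- **The analysis unit is not stated.** A reader might infer that the plan ignores course in its analysis. The article does not support that: it names no cluster unit, and an analysis plan that is not shown may include course. Only the sample size is fixed with a single level. This stands, and it makes the point about the interval conditional.
- **Mixing is inferred.** A reader might take it as stated that courses combine practices. It is not. Where course-mates share a practice, clustering on practice already absorbs their correlation. This also stands; the inference is strong, but complete mixing is an upper bound.
- **Educator effects partly cancel.** Educators deliver both arms (*Qualitative sub-studies*), so an effect common to both arms drops out in part. Not all course variance therefore reaches the comparison. What remains is the arm-specific part: group effects within a course, and an educator's preference for one method.
- **The plan limits the mechanism.** Educators are accredited, trained to keep their views from affecting delivery, and observed. Care and strip prescriptions over the 18 months come from the practice, the level already allowed for. This makes a large course ICC for HbA1c at 18 months less likely but does not make it zero.
- **The arithmetic is right.** 142 × 1.20 does give 170. The sentence is not a miscalculation and contradicts nothing; the issue is what it leaves out.

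**Conclusion.** The point holds in a limited form. The 170 per arm allows for one level of clustering, the practice, while treatment is given in arm-specific group courses that very probably cut across practices. If the analysis clusters on practice alone, any positive arm-specific course correlation across practices makes the equivalence interval too narrow, in the direction that favours equivalence.

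The size cannot be derived from the documents. Under the assumptions in step 4 it runs from slight (2% wider) to material (17% wider), and it is nil if the course ICC is 0. The top of the range combines the largest assumed course, the largest assumed ICC and complete mixing, so it should not be read as the expected shortfall. Nor do the documents show that the planned interval is wrong, because the unit for the generalised estimating equations is left open. This is a worthwhile and cheap improvement, not a demonstrated error.

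**What to change.** - Retain the course each participant attended as an identifier in the trial data. Booking should already hold it, although the article does not say that it is kept. If it is lost, later analysis cannot recover it.
- In *Statistical analysis*, name the clustering units and use variance that reflects both: either the marginal linear model with two-way cluster-robust variance for practice and course, or a linear mixed model with practice and course as crossed random effects.
- Report the ICC for each level.
- In *Power calculations and sample size*, state that 170 per arm allows for practice clustering only.

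The cost is one identifier, a few changed sentences, a little more analysis and a slightly wider interval. If course correlation proves negligible, almost nothing is lost.

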#### Statistical analysis

There will be double entry of all data and discrepant values will be investigated. Results will be reported according to CONSORT guidelines for cluster randomised trials and statistical analysis carried out on an intention-to-treat basis. Missing outcomes will not be replaced and an average over-time of continuous outcomes will be derived. This procedure will measure the cumulative effect of the treatment and have the maximum number of participants. Continuous variables will be analysed using a linear model adjusting for clustering using generalised estimating equations, and adjusting for baseline values.

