The situation is much more uncertain for individuals with T2DM, particularly those managing their condition with lifestyle adjustments or using oral agents other than sulphonylureas. This uncertainty is reflected in the wide variation in the use of SMBG in different parts of the UK, [9] but even in areas where SMBG is used less often, the estimated costs are considerable, amounting to hundreds of thousands of pounds in an average primary care trust. It has been argued that providing such technology to those on tablets or diet is a waste of time and money since there is little an individual can do with the result [10]. Others believe strongly that the information provided by SMBG is a powerful motivating factor, [11] encouraging self-management by enabling people with T2DM to measure directly the effect of different actions, such as the effect of eating on post-prandial glucose or the glucose lowering effect of exercise. Previous studies have attempted to assess the contribution of SMBG to improved metabolic control in this group. Most, [12,13] but not all, [14] observational studies have shown that even in those managing their T2DM using diet alone, increased frequency of SMBG is associated with better outcomes including lowered glycated haemoglobin (HbA1c) and less mortality. This has been used to advocate SMBG for all those with T2DM [15]. However, these results may merely indicate that those who are highly motivated (reflected in the take-up of SMBG technology) are likely to do well in the long term.

Trials of interventions incorporating education about SMBG have reported mixed results. The DIGEM study reported no evidence of an effect of SMBG (with or without support from trained practice nurses in the interpretation and application of results) [16]. However, limitations included potential contamination due to lack of cluster-randomisation, a drop in adherence to SMBG over the study period, [17] and exclusion of people with prior experience of SMBG. Similarly, the ESMON study reported no evidence of an effect of structured education with or without additional education on self-monitoring [18]. Both studies reported a net adverse effect on anxiety/depression, suggesting that SMBG increased worry and depressed mood.

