### Study objectives and outcome measures

The primary objective is to ascertain whether there are equivalent changes in HbA1c (primary outcome measure) in people with newly diagnosed T2DM allocated to either a urine or a blood glucose monitoring strategy over 18 months when incorporated as an integral part of a comprehensive self-management structured education programme (DESMOND).

The secondary objectives include: comparison of the two strategies on the secondary outcome measures over 18 months, including biomedical measures (systolic and diastolic blood pressure, lipid profile, body weight and waist circumference) and psychological measures (well being, anxiety, depression, treatment satisfaction and perceptions about diabetes) (for further details see Table 1). A qualitative sub-study will explore participant views about acceptability of, and preference for, the two self-monitoring methods included. An assessment of cost effectiveness will be conducted.

**Table 1 T1:** Biomedical and questionnaire measures used and time points in the trial

	Baseline	6 months	12 months	18 months

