### Development and piloting of self-monitoring sessions

Experienced DESMOND trainers developed and piloted the new self-monitoring sessions using an iterative cycle. Six educators from 3 PCTs were then trained in delivery of the sessions before delivering it incorporated into the DESMOND programme to patients in their area. Subsequently the educators provided feedback which led to revision of the sessions and resources.

The 6-h DESMOND structured education programme is underpinned by a philosophy and learning theories that promote adult learning through interactive step-wise processes, which increase self-efficacy to promote self-management [33]. Therefore, the newly developed monitoring sessions needed to reflect these principles.

The content of the self-monitoring sessions is summarised in Table 2. It was delivered in two separate sessions, totalling 100 min in length. They were embedded within the DESMOND education programme, which for the purpose of this study is delivered in two sessions, one to two weeks apart. Resources were developed for use within the sessions to enhance participant interaction and self confidence, support a reflective approach to self-monitoring, and identify self management changes in relation to results. The approach to self-monitoring is not directive and regimented but promotes the practice of self-monitoring as a tool to support decision making in regard to lifestyle changes and medication. Participants were encouraged to decide when and how often to monitor, how to interpret the results and to explore options for change. Although they were allocated randomly to either the blood or urine method of monitoring, they are able to swap methods or to stop monitoring if they choose. Participants were asked to report any change in method on the 6, 12 or 18 month questionnaire.

**Table 2 T2:** Contents of sessions on self-monitoring included in DESMOND programme in trial

Session 1	Monitoring and measuring blood glucose levels (20 mins)
	
	• Long term blood glucose control using HbA1c and recommended targets
	• How measurement of long term glucose control differs from self monitoring
	• Introduction to Health Profile
	
	Methods of self monitoring (20 mins) *
	
	• Purpose of self monitoring and how to use the information
	• How and when to monitor blood/urine
	• Target levels for blood/urine monitoring
	
	Purpose of self monitoring (20 mins)
	

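### An intention-to-treat equivalence result, with free swapping and stopping, supports a claim about the strategies offered but not, by itself, about blood versus urine monitoring as used

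*Protocol article*

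**What the plan says.** The primary objective (Study objectives and outcome measures) is equivalence of HbA1c change between people allocated to a urine or a blood monitoring strategy. Power calculations and sample size sets the margin at ±0.5% at 18 months.

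Statistical analysis specifies "statistical analysis carried out on an intention-to-treat basis". Outcomes are averaged over time and analysed in a baseline-adjusted linear model, with generalised estimating equations for clustering. No other analysis set is named.

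Development and piloting of self-monitoring sessions says of participants in either arm that "they are able to swap methods or to stop monitoring if they choose". The data are collected: "Participants were asked to report any change in method on the 6, 12 or 18 month questionnaire". The Discussion says that the strategies participants adopt will be measured and changes recorded, and Qualitative sub-studies covers the experience of people who swapped. None of this is tied to the equivalence conclusion.

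The conclusions reach beyond the strategy offered. Testing the hypothesis and the Discussion speak of measuring the equivalence, or added benefit, of blood glucose monitoring while controlling for feedback from the other method. Implications of the hypothesis says that an equivalence result will be used as evidence for recommending blood glucose monitoring in this population.

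**The concern.** In a superiority trial, departures from allocation usually work against the claim. In an equivalence trial, departures that make the arms alike work for it. Here they are permitted by design, so they cannot be treated as rare protocol deviations.

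The article recognises the issue in other trials. Its Background lists "a drop in adherence to SMBG over the study period" among the limitations of an earlier trial of blood glucose monitoring. It also reports a cluster-randomised trial of structured testing in which the difference was 0.3% overall and 0.5% per protocol; the second figure equals the whole margin here.

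At stake is what an equivalence result would mean. It could show that the two methods give similar control when used. It could also show only that enough people swapped or stopped for any difference to fade. The first reading bears on a recommendation about the method; the second bears only on what happens when each method is offered.

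**Working it through.** **Inputs** (Power calculations and sample size): margin 0.5%, SD 1.5%, 80% power, 5% significance, intra-cluster correlation 0.05, mean cluster size 5, 20% drop-out, 20% non-consent.

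**The plan's own figures.**
- Unclustered: 2 × [1.5 × (1.960 + 0.842) / 0.5]² = 141.3, so 142 per arm. This matches the text ("the sample size required without allowing for clustering for 80% power at 5% significance is 142 per arm").
- Design effect: 1 + (5 − 1) × 0.05 = 1.20, and 142 × 1.20 = 170.4, stated as 170.
- 170 / 0.8 = 212.5, stated as 213; 170 / 0.64 = 265.6, stated as 266.

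All reproduce. None contains an allowance for swapping or stopping.

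**Standard error at the planned size.** Effective n per arm = 170 / 1.20 = 141.7, so SE = 1.5 × √(2 / 141.7) = 0.178.

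**How departures act.** Let B and U be the effects of blood and urine monitoring against no monitoring, and D = B − U.
- *Swapping only*, by fraction a of the blood arm and b of the urine arm: intention-to-treat difference = D(1 − a − b). It shrinks.
- *Equal stopping* by fraction s in each arm: difference = D(1 − s). It shrinks.
- *Unequal stopping* by s₁ and s₂: difference = (1 − s₁)B − (1 − s₂)U. It can shrink or grow. For example, assume B = U = 0.5%, with 10% stopping in one arm and 50% in the other: 0.9 × 0.5 − 0.5 × 0.5 = 0.20%, although the methods are identical in use.

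**Illustration of the shrinking cases.** The article gives no swap or stop rate, so the dilution f is assumed. It equals a + b for swapping, or s for equal stopping. Take a true difference under use of 0.5%, so that t = 0.5(1 − f), and

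P(equivalence) = Φ((0.5 − t)/SE − z) + Φ((0.5 + t)/SE − z) − 1,

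with z = 1.645 for a 90% interval and 1.960 for a 95% interval.

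| Assumed f | t | 90% interval | 95% interval |
|---|---|---|---|
| 0% | 0.50% | 5.0% | 2.5% |
| 20% | 0.40% | 13.9% | 8.0% |
| 30% | 0.35% | 21.0% | 12.9% |
| 40% | 0.30% | 29.8% | 19.5% |

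Worked row, f = 20%, 90% interval: (0.5 − 0.4)/0.178 − 1.645 = −1.08, so Φ = 0.139; the other two terms cancel almost exactly. At f = 30%, a difference under use of 0.5 / 0.7 = 0.71% would sit on the margin.

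Both intervals are shown because the article does not say whether its 5% is per side or in total.

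**Precision of an analysis restricted to continuing users.** Assume 30% are excluded: 170 × 0.7 = 119 per arm, cluster size 3.5, design effect 1 + 2.5 × 0.05 = 1.125, effective n = 105.8, SE = 1.5 × √(2 / 105.8) = 0.206. The probability that the interval lies within the margin when the true difference is zero, 2Φ(0.5/SE − z) − 1, falls from about 75% to 56% (90% interval) or from about 60% to 36% (95% interval).

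**The case against.** The strongest defence is that intention-to-treat answers the question posed. The objective compares people allocated to strategies, participants choose when and how often to monitor, and the Discussion calls the trial pragmatic. Swapping and stopping are then part of the effect. This stands, so a reader who inferred that intention-to-treat is the wrong primary analysis would go further than the document allows.

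A reader might also infer that the plan excludes any other analysis. It does not: it names one basis and is silent on others, and a statistical analysis plan that is not shown may add one. Silence is not the point. What is stated is the pairing of that basis with conclusions about blood glucose monitoring itself.

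Nor can it be said that departures always favour equivalence, since unequal stopping can widen the difference. The dilution rates are assumed and nothing in the article anchors them. The 0.3% versus 0.5% contrast in the Background is no proof of dilution, because a per-protocol set is selected.

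Finally, a supportive analysis has weaknesses of its own. The Background warns that good results among people who self-monitor may merely reflect motivation, and a set of persistent users invites that selection. Requiring both analyses to meet the margin would also be costly, as the power figures show. These objections rule out a second formal gate, but they leave the mismatch between analysis and conclusion in place.

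**Conclusion.** The point holds in limited form. Intention-to-treat is sound for equivalence of the strategies as offered. By itself it does not support the conclusions about blood glucose monitoring in Testing the hypothesis, Implications of the hypothesis and the Discussion, because the design permits departures that can produce apparent equivalence.

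The illustrative size is a rise from 5% to 14–30%, or from 2.5% to 8–20%, in the chance of declaring equivalence when the difference under use is exactly 0.5%. This assumes 20% to 40% dilution from swapping or from similar stopping in both arms, and the planning SD, correlation and cluster size. These are errors only with respect to the methods as used. The direction is not settled if stopping differs between arms.

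This is a worthwhile, low-cost improvement and does not invalidate the primary analysis.

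**What to change.** No change to participants' freedom to swap or stop is suggested. The changes concern analysis and wording.

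1. Keep intention-to-treat as the primary analysis and word its conclusion as equivalence, within ±0.5% HbA1c, of the strategies offered. Align Testing the hypothesis, Implications of the hypothesis and the Discussion with that wording.
2. Pre-specify a supportive analysis of participants still using the allocated method at 6, 12 and 18 months, with the same baseline-adjusted estimating-equation model. Use the method-change data already collected. Define continued use in advance, and confirm that the questionnaire item captures stopping as well as swapping.
3. Report swap and stop rates by arm at each follow-up, so that readers can judge whether departures were balanced.
4. Interpret the two analyses together. Extend the claim to the methods as used only if they are consistent, without making the supportive result a second formal test.

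**Cost.** No new data collection, provided the item captures stopping. The supportive set is selected and self-reported, and its interval is wider (SE about 0.206 against 0.178 if 30% are excluded). A complier-average estimate could be added, but there are three states (blood, urine, none) and one binary instrument, so it needs further assumptions that would have to be stated.

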**Methods/Design:**

The DESMOND SMBG trial is comparing two monitoring strategies (blood glucose monitoring and urine testing) over 18 months when incorporated into a comprehensive self-management structured education programme. It is a multi-site cluster randomised controlled trial, conducted across 8 sites (7 primary care trusts) in England, UK involving individuals with newly diagnosed Type 2 diabetes.

The trial has 80% power to demonstrate equivalence in mean HbA1c (the primary end-point) at 18 months of within ± 0.5% assuming 20% drop out and 20% non-consent. Secondary end-points include blood pressure, lipids, body weight and psychosocial measures as well as a qualitative sub-study.

Practices were randomised to one of two arms: participants attend a DESMOND programme incorporating a module on self-monitoring of either urine or blood glucose. The programme is delivered by accredited educators who received specific training about equipoise. Biomedical data are collected and psychosocial scales completed at baseline, and 6, 12, and 18 months post programme. Qualitative research with participants and educators will explore views and experiences of the trial and preferences for methods of monitoring.

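### The margin, SD and sample size are for HbA1c at 18 months, but the planned analysis is of each person's average over follow-up, so a difference that emerges late could be passed as equivalence

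*Protocol article*

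**What the plan says.** Two sections of the protocol article fix the target at a single time point. The Abstract (Methods/Design) names "equivalence in mean HbA1c (the primary end-point) at 18 months" and attaches the ±0.5% margin to it. Power calculations and sample size repeats this, "The aim is to show equivalence in mean HbA1c at 18 months of within ± 0.5" (in % HbA1c), and draws the variability from the same visit: "Assuming a standard deviation (SD) at 18 months of 1.5" (again %).

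The Statistical analysis section then fixes a different outcome variable: "Missing outcomes will not be replaced and an average over-time of continuous outcomes will be derived". Its reason follows: "This procedure will measure the cumulative effect of the treatment and have the maximum number of participants". The average goes into a linear model with generalised estimating equations (GEE) for clustering and adjustment for baseline. HbA1c is continuous and, by Table 1, is measured at baseline and at 6, 12 and 18 months. The section neither exempts HbA1c from averaging nor describes an 18-month contrast.

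Other wording leans towards the whole period. Study objectives and outcome measures, and Presentation of the hypothesis, speak of HbA1c change and glycaemic control over an 18-month span rather than at its end.

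**The concern.** An average of the 6, 12 and 18-month values estimates something other than the 18-month mean. In an equivalence trial, anything that shrinks a real difference towards zero favours the claim being tested. If the arms separate late, the earlier visits pull the estimate inside the margin even though the 18-month difference lies at or beyond it.

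Late separation is not far-fetched on the document's own account. Participants may change method or stop monitoring (Development and piloting of self-monitoring sessions), and the Background counts falling adherence to blood monitoring among the limitations of an earlier trial. The consequence is practical too: under Implications of the hypothesis, a finding of equivalence would support recommending blood monitoring.

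Missing visits add to the problem. Values are not replaced, the stated aim is to keep as many participants as possible, and someone who misses a visit is approached at the next. The natural reading is that each person is averaged over whatever visits they have. Someone lost after 6 months would then contribute a 6-month value standing in for the full-period average.

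**Working it through.** **The plan's own figures.** Inputs from Power calculations and sample size: margin 0.5, SD 1.5, 80% power, 5% significance, intra-cluster correlation 0.05, mean cluster size 5, 20% dropout, 20% non-consent.

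- Unclustered: 2 × (1.96 + 0.84)² × 1.5² / 0.5² = 141.3, so 142 per arm.
- Design effect: 1 + (5 − 1) × 0.05 = 1.2; 142 × 1.2 = 170.4, stated as 170.
- Consents: 170 / 0.8 = 212.5, so 213. Referrals: 213 / 0.8 = 266.25, stated as 266.

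All four reproduce, and all rest on the 18-month SD and margin. None uses the SD of an average.

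**Standard errors.** Effective size per arm is 170 / 1.2 = 141.7.

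- 18-month difference: SE = 1.5 × √(2 / 141.7) = 0.178.
- Average of three complete visits: SE = 0.178 × √((1 + 2ρ) / 3), where ρ is the between-visit correlation. The document gives no ρ; 0.5 to 0.7 is assumed. This gives 0.146, 0.153 and 0.159 for ρ = 0.5, 0.6 and 0.7.

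**Probability of declaring equivalence** when the true difference in the analysed quantity is μ (confidence interval wholly inside ±0.5, normal approximation, no gain taken from baseline adjustment):

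P = Φ((0.5 − z·SE − μ) / SE) − Φ((−0.5 + z·SE − μ) / SE)

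The 5% level is not tied to a CI width, so both z = 1.96 (95% CI) and z = 1.645 (90% CI) are shown.

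Example: a difference growing linearly from zero to 0.5 is 0.167, 0.333 and 0.5 at the three visits, so the average is (0.167 + 0.333 + 0.5) / 3 = 0.333. With ρ = 0.5 and a 95% CI, the estimate must be below 0.5 − 1.96 × 0.1455 = 0.215. Then (0.215 − 0.333) / 0.1455 = −0.81, and P = 0.208.

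Probability that equivalence is declared (ranges are over ρ = 0.5 to 0.7):

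| True difference at 6 / 12 / 18 months (%) | Average | 18-month analysis, 95% CI | Planned average, 95% CI | 18-month analysis, 90% CI | Planned average, 90% CI |
|---|---|---|---|---|---|
| 0.167 / 0.333 / 0.5 | 0.333 | 2.5% | 18–21% | 5% | 27–31% |
| 0 / 0.25 / 0.5 | 0.25 | 2.5% | 34–40% | 5% | 47–53% |
| 0.2 / 0.4 / 0.6 | 0.4 | 0.6% | 9–10% | 1.4% | 15–17% |
| 0.5 / 0.5 / 0.5 | 0.5 | 2.5% | 2.5% | 5% | 5% |
| 0.75 / 0.375 / 0 | 0.375 | 60% | 12–14% | 75% | 19–22% |
| 0 / 0 / 0 | 0 | 60% | 76–86% | 75% | 86–93% |

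The first three rows are the harmful case. The fourth shows no effect, and the fifth shows the opposite bias. The last row is power when the arms do not differ.

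**Missing 18-month values.** Suppose 20% have the 6 and 12-month values only (an assumption; the stated dropout figure carries no time point). In the 0 / 0.25 / 0.5 pattern, these people average 0.125, and the overall mean falls from 0.25 to 0.8 × 0.25 + 0.2 × 0.125 = 0.225.

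**The case against.** The strongest reply is that the average may be intended. The primary objective and the null hypothesis are worded over the 18-month period, and the analysis section gives a reason for averaging: a cumulative effect. On that view the Abstract and the sample-size section are loosely worded and the analysis is right. This stands in part, because the document does hold two competing targets and the choice belongs to the sponsor. It does not remove the inconsistency. The Abstract labels the 18-month mean as the primary endpoint, and no margin, SD or sample size is given for an average.

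A second reply is that the harm is conditional. That stands in full. A reader might infer that averaging always favours equivalence, or that this plan has a false-equivalence rate of about 20%. The documents support neither: they give no trajectory and no between-visit correlation, a constant difference is not diluted, and a fading one is penalised.

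Third, averaging over available visits is a strong inference, not a statement in the text. Weighting and any minimum number of visits may be settled in an analysis plan. Unequal variances among such averages are a lesser matter: with robust GEE standard errors (not stated here) they would cost efficiency rather than validity.

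Finally, the average is more precise, so giving it up has a real cost in power.

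**Conclusion.** The point holds as a stated mismatch. The endpoint, margin and SD are defined at 18 months, and the only analysis described estimates an average over follow-up. This is not a detail left to a fuller document, because the article itself fixes the outcome variable and gives the reason for it.

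The two analyses can lead to opposite conclusions. With a true 18-month difference at the margin and linear growth from zero, false equivalence is about 18–21% instead of 2.5% (95% CI), or 27–31% instead of 5% (90% CI). With an early difference that has vanished by 18 months (0.75 / 0.375 / 0), the average finds equivalence 12–14% of the time against 60% (95% CI). These figures rest on assumed trajectories, complete visits, ρ of 0.5 to 0.7 and the planned 170 per arm. They illustrate the size of the problem and do not predict this trial's error rate. The direction for a late-emerging difference does not depend on ρ.

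**What to change.** Name one primary quantity before results are seen, and make the Abstract, objectives, sample-size and analysis sections agree on it.

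Preferred: judge equivalence on the baseline-adjusted 18-month arm contrast against ±0.5%, from a repeated-measures model of the 6, 12 and 18-month values with visit, arm, arm-by-visit and baseline terms and clustering by practice. Anyone with follow-up data still contributes, so the aim of keeping participants is met. A likelihood-based mixed model is preferable: it needs outcomes missing at random, whereas unweighted GEE generally needs them missing completely at random. Keep the time-average as a secondary analysis. The stated 142 / 170 / 213 / 266 need no change on this account, since they already use the 18-month SD and margin.

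Alternative: declare the average primary in the Abstract and the sample-size section, re-justify margin, SD and sample size for it, and state how incomplete follow-up enters.

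Cost: the preferred change needs new analysis wording and a little code, with no new data. It gives a wider interval. With no true difference, power is about 60% rather than 76–86% (95% CI), or 75% rather than 86–93% (90% CI), before any gain from baseline adjustment and earlier visits. That the 18-month figures fall below the stated 80% is a separate matter: 142 follows from a superiority or one-sided non-inferiority formula, whereas an equivalence formula with true difference zero gives 155 (90% CI) or 190 (95% CI) per arm before clustering.
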